# **1 INTRODUCTION**

This statistical analysis plan (SAP) details the planned statistical analyses for the “Effect of Cerebellar Stimulation on the Awareness Recovery in Disorders of Consciousness: A randomized, controlled, double-blind, cross-over trial.” It is based on the protocol, as well as any subsequent amendments. The SAP should be read together with the protocol.

## **2 STUDY OBJECTIVES AND OUTCOMES**

### **2.1 Study objectives**

#### **2.1.1 Primary objective(s)**

To evaluate the effect of 5-session bilateral cerebellar iTBS stimulation on promoting consciousness recovery in patients with DoC.

#### **2.1.2 Secondary objective(s)**

- To evaluate the effects of cerebellar iTBS on EEG after five treatment sessions.
- To assess the functional outcomes of all the participants at 3 months and 6 months after enrolment.

### **2.2 Study outcomes**

#### **2.2.1 Primary outcome(s)**

- Difference in the change of CRS-R total score between the iTBS and sham stimulation groups after five treatment sessions.

#### **2.2.2 Secondary outcome(s)**

- The between-group difference in the change of CRS-R subscale scores after five treatment sessions.
- The between-group difference in the “ABCD” EEG patterns and PSD after five treatment sessions.

#### **2.2.3 Follow-up outcome (s)**

- GOS-E scores at 3 months and 6 months after enrolment.

### **2.2.4 Safety outcome(s)**

Safety outcomes included adverse events, including intolerance to TMS, and severe adverse events. The common adverse effects of TMS include dizziness, headache, tinnitus, and tingling or burning sensation on the scalp, which usually ease spontaneously without symptomatic treatment. Any uncomfortable condition due to the iTBS stimulation and needs to be eased by down-regulating stimulus intensity or discontinuation of stimulation are seen as intolerance. Rare adverse effect of TMS includes seizures, for which physicians will administer appropriate symptomatic treatment.

A Serious Adverse Event (SAE) is defined as any event that:

- requires inpatient treatment not envisioned in the protocol or extends a current hospital stay;
- results in permanent or significant incapacity or disability;
- is life-threatening or results in death;
- causes a congenital anomaly or birth defect.

## **3 STUDY DESIGN**

This will be a randomized, double-blind, crossover trial. Patients will be randomly assigned to the iTBS stimulation-first group or the sham stimulation-first group after the 5-day baseline assessments. During each treatment session, patients will receive either active stimulation or sham stimulation once daily for 5 consecutive days. The two treatment sessions are separated by a 5-day washout period. Demographic, MRI, and clinical characteristics of the patients will be collected at enrolment. The CRS-R score will be assessed before and after every session of active and sham stimulation within 2 hours. 32-channel EEG will be performed 20 minutes before and after the first and after the fifth treatment sessions within 30 minutes. The analyses will compare the effects of iTBS and sham stimulation on the CRS-R score and EEG and assess the functional outcomes of all the participants 3 months and 6 months after enrolment.

## **4 DETERMINATION OF SAMPLE SIZE**

We determined that enrolling 44 patients would provide 90% power to detect a mean difference of 1.2 points (standard deviation [SD] = 1.5) in CRS-R changes between the active and sham stimulation groups, using a two-sided  $\alpha$  of 0.05 and accounting for a 15% dropout rate. The anticipated  $1.2 \pm 1.5$ -point difference was conservatively estimated based on previous studies.

### **4.1 Analysis populations**

Analyses of primary outcomes will be conducted in the ITT population and repeated in the PP population. The ITT population will include all patients who are randomized and the PP population will include all subjects who are randomized and do not deviate from the treatment procedure.

## 5 MISSING DATA

For the ITT population, missing data are imputed using the LOCF method. The patients who drop out before the cessation of the last intervention will be excluded from the PP analyses.

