## **5 RANDOMIZATION**

Once informed consent has been provided, the investigator should obtain the result of the randomization. Based on the random number table without stratification or blocks, patients will be assigned to one of the two intervention groups (1:1 ratio): iTBS stimulation-first or sham stimulation-first group.

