The analysis will be conducted in the intention-to-treat (ITT) populations and repeated in the per-protocol (PP) populations to test the robustness. For the ITT population, missing data will be imputed using the last observation carried forward method. EEG analyses will be performed in patients with valid EEG data, and adjustments for multiple comparisons will be conducted using the false discovery rate method. Two-sided P-values  $< 0.05$  were considered statistically significant. All statistical analyses will be performed using PASS 20.0 (NCSS, LLC, Kaysville, UT,

USA), R version 4.3.0 and SPSS version 26 (SPSS Inc., Chicago, IL, USA).

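### The LOCF rule for the ITT analysis is not confined to a treatment period, so a patient with no period-2 data is filled from the other treatment and the primary estimate is attenuated

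*Supplement*

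**What the plan says.** The primary outcome in SAP V2.0 section 2.2.1 is: "Difference in the change of CRS-R total score between the iTBS and sham stimulation groups after five treatment sessions". Section 4.1 defines the ITT population as everyone randomised and runs the primary analysis in it, with a repeat in the per-protocol (PP) population.

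On missing data, SAP section 5 says "For the ITT population, missing data are imputed using the LOCF method", and section 6 says "For the ITT population, missing data will be imputed using the last observation carried forward method". Protocol V2.0 sections 13.2 and 13.3 carry the same rule. Patients who leave before the last intervention ends are dropped from the PP analysis.

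The design (SAP section 3) gives every patient both treatments in turn: "The two treatment sessions are separated by a 5-day washout period". CRS-R is scored before and after each daily session, and the text describes no CRS-R assessment in the washout. The sample size in SAP section 4 is stated as "accounting for a 15% dropout rate".

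Three things are not stated: whether a value may be carried from period 1 into period 2, whether the score or the change is carried, and whether change is measured from the period's own baseline or from enrolment.

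**The concern.** In a parallel-group trial, LOCF carries a value observed under the same treatment. In a crossover, a patient who leaves before any period-2 score has a last value from the other treatment. If the change is carried, the patient's iTBS-sham contrast becomes exactly 0 by construction. If the score is carried and change is taken from the period baseline, the pre and post scores of period 2 are equal and the period-2 change becomes 0. Either way, a contrast that was never observed enters the primary analysis as data.

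At stake are the size of the reported effect and the placement and width of its confidence interval. The rule is also ambiguous: the same sentence permits two analyses with different expected results. The plan's linear mixed model (LMM) has a random subject effect and can use a patient with one period directly, so the imputation is not needed to keep such patients in the ITT analysis.

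**Working it through.** **Inputs.** From SAP section 4: "enrolling 44 patients would provide 90% power to detect a mean difference of 1.2 points (standard deviation [SD] = 1.5) in CRS-R changes", two-sided alpha 0.05, 15% dropout. From protocol section 5: two sequences, 1:1. Assumptions of this check: SD 1.5 is the SD of one period's change and the two changes are independent, so the within-patient contrast has variance 2 × 1.5² = 4.5; a fraction p of patients has no period-2 score, completely at random and equally in both sequences; the sham change is 0.5 where it is needed.

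**The plan's own figure.** For a 2×2 crossover with contrast SD 1.5 × √2 = 2.121, the noncentral t gives 35 completers (36 if even). 35/0.85 = 41.2, so 42; 36/0.85 = 42.4, so 43, or 44 rounded to even. With 37 completers (44 × 0.85 = 37.4) power is 0.917. This is within 2 patients of 44. Reading 1.5 as the SD of the paired difference gives only 23-24 enrolled, so the first reading is used.

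**Reference standard errors.** No missing data: √(4.5/44) = 0.320. Completers at p = 0.15: √(4.5/37.4) = 0.347 (0.345 in simulation).

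**Change carried.** Incomplete patients contribute 0.
- Mean: 0.85 × 1.2 + 0.15 × 0 = 1.02.
- SE: √[(0.85 × 4.5 + 0.85 × 0.15 × 1.2²)/44] = √(4.009/44) = 0.302.

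**Score carried.** An incomplete iTBS-first patient contributes (0.5 + 1.2) − 0 = 1.7 on average; an incomplete sham-first patient contributes 0 − 0.5 = −0.5. Their mean is 0.6. The sham change cancels because dropout is equal.
- Mean: 0.85 × 1.2 + 0.15 × 0.6 = 1.11.
- Variance, iTBS-first: 3.825 + 0.15 × 2.25 + 0.1275 × 0.5² = 4.194. Sham-first: 3.825 + 0.3375 + 0.1275 × 1.7² = 4.531. Average 4.363.
- SE: √(4.363/44) = 0.315.

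**Coverage of 1.2 (normal approximation).** Change carried: shift/SE = 0.18/0.302 = 0.60, so Φ(1.36) − Φ(−2.56) = 0.908. Score carried: 0.09/0.315 = 0.29, so Φ(1.67) − Φ(−2.25) = 0.940. Simulation gave about 90% and 94%.

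**Simulation summary at p = 0.15** (6000 runs; the LMM from 200 REML fits):

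| Analysis | Mean estimate | SE | Coverage of 1.2 | Power |
|---|---|---|---|---|
| Observed-data LMM | 1.20 | about 0.34 | not tabulated | not tabulated |
| Completers | 1.20 | 0.345 | 95% | 92.4% |
| LOCF, score carried | 1.11 | 0.31 | about 94% | 93.5% |
| LOCF, change carried | 1.02 | 0.30 | about 90% | 91.4% |

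Under the null, LOCF rejected in 4.6% to 5.1% of runs. The model SE matched the sampling SD of each LOCF estimator: 0.313 against 0.315 (score) and 0.300 against 0.302 (change).

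**Sensitivity.**
- At p = 0.05: 1.2 × 0.95 = 1.14 (change) and 1.2 × 0.975 = 1.17 (score). With the change carried, SE is 0.314 against 0.328 for completers.
- If 1.5 is the SD of the paired difference, the change-carried mean is still 1.02, with SE 0.218 against 0.245.
- Unequal dropout by sequence (assumed 25% and 5%), 1 point of spontaneous change per period, no true effect, score carried: (0.25 × 1 − 0.05 × 1)/2 = 0.10, with the sign set by which sequence loses more. Rejection was 5.7% to 6.4%.

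**The case against.** **A within-period reading is open.** CRS-R is taken around every session, so a patient who leaves mid-period has a same-treatment score to carry. One could also read the rule as stopping at the period boundary, in which case a patient with no period-2 score would simply contribute period 1 to the LMM. This stands as far as it goes: the cross-treatment fill affects only patients with no period-2 data, and the documents do not say how many those would be. But the SAP does not set that boundary, and its rule applies to missing ITT data without restriction.

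**The decision hardly moves.** Under equal random dropout the bias is toward the null, type I error is near nominal, and power is within about one percentage point of the completer analysis. This stands.

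**The standard error is not wrong for its estimator.** A reader might infer that LOCF makes the reported SE invalid. The calculation does not support that: each LOCF SE matches its own sampling SD. What holds is narrower. The interval is centred on an attenuated value, and its SE (0.30-0.31) is smaller than the observed data support (0.345 for completers). The loss of coverage comes mainly from the shifted centre.

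**LOCF is not biased in every scenario.** When the 15% with the largest period-1 change are assumed to leave, score-carried LOCF averages 1.20, the true value, while change-carried LOCF gives 0.87 and completers 0.995. So a general claim that LOCF is biased either way fails. The observed-data LMM was not run in that scenario, so no advantage is claimed for it there.

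**The PP repeat is a check.** It excludes early leavers and under random loss is roughly the completer analysis, so a gap from the ITT result would be visible. It does not repair the primary ITT estimate, and it discards the period-1 data of those patients.

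**Conclusion.** The point holds as a should-fix. As written, the rule allows period-1 data from one treatment to stand in for period 2 under the other, in the primary analysis and primary population, and it does not define what is carried. With the plan's figures and the whole 15% lost at random before any period-2 score, a true 1.2 is estimated as 1.02 (15% attenuation, coverage about 90%) or 1.11 (7.5%, about 94%). That is an upper case under the plan's own dropout figure; with 5% wholly missing the attenuation is 5% or 2.5%.

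These sizes rest on SD 1.5 being the per-period SD, on equal random dropout and, for the score-carried SE and coverage, on an assumed sham change of 0.5.

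A reader might go further and infer an inflated false-positive rate. The check does not show that under equal random dropout. Bias in either direction needs dropout that is unequal between sequences or informative, and the one null scenario run with unequal dropout gave a spurious effect of about 0.10 and at most 6.4% rejection. The finding concerns the size of the effect, its interval and an under-specified rule.

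**What to change.** In SAP sections 5 and 6 and protocol sections 13.2 and 13.3, replace LOCF as the primary handling of missing CRS-R data. State that the primary ITT analysis is the planned LMM, fitted by REML to all observed CRS-R changes of all randomised patients, so that a patient with one period contributes that period under a missing-at-random assumption. State which baseline the change is measured from.

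If LOCF is kept, make it a sensitivity analysis confined to within a period, and say whether the score or the change is carried. Report by sequence how many patients have no period-2 score and how many leave mid-period. Multiple imputation or a delta-adjusted analysis is optional; with about 7 incomplete patients expected (0.15 × 44 = 6.6) it need not be required.

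The cost is an amendment to the wording and a few lines of code, with no new patients, visits or data.

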## 6 EFFICACY ANALYSIS

Continuous variables will be expressed as mean  $\pm$  standard deviation (SD) or median (interquartile range, IQR), and categorical variables will be expressed as percentages. Baseline continuous variables will be analyzed using Student's t-test for normal distribution and Mann - Whitney U test for skewed distribution. Categorical variables will be analyzed using  $\chi^2$  test analysis and Fisher's exact tests, when appropriate.

Besides the primary and secondary outcomes mentioned above, we will conduct a post-hoc analysis of the changes in CRS-R scores and EEG after the first treatment session. At three- and six-months post-treatment, the consciousness of patients will be additionally assessed based-on CRS-R via telephone interview.

The between-group differences in the change of CRS-R total and subscale scores after the first and fifth treatment sessions will be analyzed using a linear mixed model (LMM) with fixed effects (sequence, period, time since injury, etiology, and age) and random effects (subjects for repeated measurements).

The effects of cerebellar iTBS on CRS-R total scores will be further analyzed in subgroups of patients according to their baseline characteristics, i.e., VS/UWS and MCS, as well as anoxia etiology and non-anoxia etiology.

The between-group differences in PSD after the first and fifth treatment sessions will also be analyzed via LMM, incorporating baseline PSD as a fixed effect alongside other fixed and random variables as above.

The cumulative link mixed effects model (CLMM), which incorporated fixed and random effects as those of LMM (fixed effects: sequence, period, time since injury, etiology, and age; random effects: subjects for repeated measurements) and added baseline "ABCD" EEG patterns as fixed effects, will be used to analyze the between-group differences in "ABCD" EEG patterns after the first and fifth treatments.

We will use the ordinal logistic regression to explore the relationships between the baseline "ABCD" EEG patterns and the functional outcomes and recovery of consciousness six months post-treatment. To investigate the relationships between EEG responsiveness and six-month outcomes, we will use the generalized linear model (GLM), with adjustments made for baseline characteristics and time period.

The analysis will be conducted in the intention-to-treat (ITT) populations and repeated in the per-protocol (PP) populations to test the robustness. For the ITT population, missing data will be imputed using the last observation carried forward method. EEG analyses will be performed in patients with valid EEG data, and adjustments for multiple comparisons will be conducted using the false discovery rate method. Two-sided P-values  $< 0.05$  were considered statistically significant. All statistical analyses will be performed using PASS 20.0 (NCSS, LLC, Kaysville, UT,

USA), R version 4.3.0 and SPSS version 26 (SPSS Inc., Chicago, IL, USA).

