### 13.2 Planned Analyses

Continuous variables will be expressed as mean  $\pm$  standard deviation (SD) or median (interquartile range, IQR), and categorical variables will be expressed as percentages. Baseline continuous variables will be analyzed using Student's t-test for normal distribution and Mann - Whitney U test for skewed distribution. Categorical variables will be analyzed using  $\chi^2$  test analysis and Fisher's exact tests, when appropriate.

Besides the primary and secondary outcomes mentioned above, we will conduct a post-hoc analysis of the changes in CRS-R scores and EEG after the first treatment session. At three- and six-months post-treatment, the consciousness of patients will be additionally assessed based-on CRS-R via telephone interview.

The between-group differences in the change of CRS-R total and subscale scores after the first and fifth treatment sessions will be analyzed using a linear mixed model (LMM) with fixed effects (sequence, period, time since injury, etiology, and age) and random effects (subjects for repeated measurements).

The effects of cerebellar iTBS on CRS-R total scores will be further analyzed in subgroups of patients according to their baseline characteristics, i.e., VS/UWS and MCS, as well as anoxia etiology and non-anoxia etiology.

The between-group differences in PSD after the first and fifth treatment sessions will also be analyzed via LMM, incorporating baseline PSD as a fixed effect alongside other fixed and random variables as above.

The cumulative link mixed effects model (CLMM), which incorporated fixed and random effects as those of LMM (fixed effects: sequence, period, time since injury, etiology, and age; random effects: subjects for repeated measurements) and added

baseline “ABCD” EEG patterns as fixed effects, will be used to analyze the between-group differences in “ABCD” EEG patterns after the first and fifth treatments. We will use the ordinal logistic regression to explore the relationships between the baseline “ABCD” EEG patterns and the functional outcomes and recovery of consciousness six months post-treatment. To investigate the relationships between EEG responsiveness and six-month outcomes, we will use the generalized linear model (GLM), with adjustments made for baseline characteristics and time period.

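### The efficacy models should name treatment as a fixed effect, and the primary CRS-R model should adjust for each period's pre-treatment score

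*Supplement*

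**What the plan says.** SAP V2.0 section 2.2.1 makes the primary outcome the iTBS–sham difference in change of CRS-R total after five sessions. Section 6 analyses it with a linear mixed model (LMM) "with fixed effects (sequence, period, time since injury, etiology, and age) and random effects (subjects for repeated measurements". The cumulative link mixed model (CLMM) for the ABCD patterns repeats the list, in protocol V2.0 section 13.2 as well: "fixed effects: sequence, period, time since injury, etiology, and age; random effects: subjects for repeated measurements", plus the baseline pattern. The PSD model is built by "incorporating baseline PSD as a fixed effect alongside other fixed and random variables as above".

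Two things are absent. Treatment appears in none of the three lists. The CRS-R model has no pre-treatment CRS-R term, whereas both EEG models carry their own baseline. The score exists: SAP section 3 states "The CRS-R score will be assessed before and after every session of active and sham stimulation within 2 hours".

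Section 6 does not say which pre-treatment score defines change. Protocol V2.0 section 8.1 defines baseline consciousness as the best of two or more assessments at enrolment, which is a single value per patient.

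**The concern.** In a 2×2 crossover the treatment effect is the sequence-by-period interaction. A model with only the two main effects has no parameter for it, and its one group-like term, sequence, compares iTBS-first with sham-first patients. The word group does not settle the matter by itself: protocol section 5 applies it to the two sequences, while SAP section 2.2.1 applies it to iTBS and sham. An analyst should not have to infer the primary parameter.

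The second matter is precision. Age, etiology and time since injury are constant within a patient, so with complete data they cannot reduce the error of a within-patient contrast. The pre-treatment score of each period can, and a raw change score carries the noise of both the pre and the post measurement.

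**Working it through.** **Reproducing the plan's sample size.** SAP section 4 states that "enrolling 44 patients would provide 90% power" for "a mean difference of 1.2 points (standard deviation [SD] = 1.5) in CRS-R changes between the active and sham stimulation groups", two-sided alpha 0.05, 15% dropout. Read SD 1.5 as the SD of one period's change, with changes uncorrelated between periods. Then SE = 1.5 × √(2/N), and a noncentral t with N − 2 df gives 35 completers, or 36 when balanced (power 0.909). Per sequence, 18/0.85 = 21.2, rounded up to 22, so 44 in total. The other readings do not give 44: SD of the paired difference needs 17 (normal) or 19 (t), inflated to 20 or 23; parallel arms need 66, inflated to 78. The plan's figure therefore reproduces with no baseline adjustment.

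**Estimability.** Put a pure 1.2-point iTBS effect in the four cells:

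| | Period 1 | Period 2 | Mean |
|---|---|---|---|
| iTBS-first | 1.2 | 0 | 0.6 |
| Sham-first | 0 | 1.2 | 0.6 |
| Mean | 0.6 | 0.6 | |

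Both sequence means are 0.6 and both period means are 0.6. The sequence and period coefficients are zero, and the whole effect is left in residuals of ±0.6. The fixed-effect rank is 3 (intercept, sequence, period), and 4 once treatment is added. In simulation with the treatment term, the mean estimate was 1.19 to 1.22.

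**Precision.** Take change from the pre-session-1 score of the same period, equal pre and post within-patient error variance s², and periods independent given the patient. Let rho be the pre/post correlation of those within-patient errors. It is not in the documents, so a range is shown.

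- Variance of the change-score contrast is proportional to 4s²(1 − rho).
- Variance of the baseline-adjusted contrast is proportional to 2s²(1 − rho²).
- Ratio = (1 + rho)/2, so the reduction is (1 − rho)/2.

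With 44 × 0.85 ≈ 37 completers, the change-score SE is 1.5 × √(2/37) = 0.349 and power is 91.7% (35 df). The adjusted SE is 0.349 × √((1 + rho)/2), with 34 df:

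| rho (assumed) | Variance reduction | SE | Power |
|---|---|---|---|
| 0 | 50% | 0.247 | 99.7% |
| 0.5 | 25% | 0.302 | 97.1% |
| 0.8 | 10% | 0.331 | 94.1% |
| 0.9 | 5% | 0.340 | 92.9% |
| 0.95 | 2.5% | 0.344 | 92.3% |

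Simulated variance ratios with 38 completers were 0.53 at rho 0, 0.74 to 0.76 at 0.5, 0.94 at 0.8 and 0.98 at 0.9. Most lie a little above theory, because a slope has to be estimated, so the table is slightly optimistic.

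**Carryover.** Suppose a residual iTBS effect L persists unchanged through period 2 in iTBS-first patients. It raises both the pre and the post score of that period and cancels from the change. In the adjusted analysis it shifts the baseline contrast between sequences, and the bias is −(1 − rho)L/2. For a true effect of 1.2 and assumed values of L:

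| L | Change score | Adjusted, rho 0 | rho 0.5 | rho 0.8 |
|---|---|---|---|---|
| 0 | 1.20 | 1.20 | 1.20 | 1.20 |
| 0.6 | 1.20 | 0.90 | 1.05 | 1.14 |
| 1.2 | 1.20 | 0.60 | 0.90 | 1.08 |

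**The case against.** A reader might infer that the trial will fail to estimate its primary contrast. The documents do not support that. The sentence holding the term list says that the model analyses differences between groups in CRS-R change, and SAP section 2.2.1 identifies those groups as iTBS and sham. The list can be read as the terms that accompany the comparison. This is a gap in specification, and naming the term closes it.

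A reader might also take the loss of efficiency to be at least 10%, or the sample size to be undermined. Neither follows. A floor of 10% needs rho no higher than 0.8; at 0.95 the loss is 2.5%. Change is a legitimate prespecified outcome that already uses the pre-treatment score, and unadjusted power at 37 completers is about 92%, above the planned 90%. Baseline terms in the EEG models do not oblige the CRS-R model to have one.

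The strongest objection is that adjustment has a price. The period-2 pre-treatment score is taken after the first treatment with only a 5-day washout, and the Background section of the protocol credits repetitive stimulation with lasting plasticity. The bias formula above is correct, and the bias is greatest where the precision gain is greatest. If the residual effect fades during period 2, the change score is biased too, so neither analysis dominates. This part of the objection stands and shapes the fix.

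**Conclusion.** The point holds in two parts of unequal weight. First, all three efficacy models omit treatment from their listed fixed effects, and read literally the lists do not yield the intended iTBS–sham estimate. Intent is clear from the surrounding text, so this is a wording defect, but it concerns the primary parameter and should be corrected.

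Second, leaving out the period-specific pre-treatment CRS-R gives up (1 − rho)/2 of the variance: between 2.5% and 50% for rho from 0.95 down to 0. That is an available gain in precision. It rests on an assumed rho, equal pre and post variances, SD 1.5 as the per-period change SD, and no carryover. The gain needs the period-specific score; the single enrolment score is constant within a patient and would add nothing to the within-patient contrast in complete data.

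**What to change.** In SAP section 6 and protocol section 13.2:

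- List treatment (iTBS vs sham) as a fixed effect in the CRS-R LMM, the PSD LMM and the CLMM.
- Name the treatment coefficient from the CRS-R total model, with its 95% CI, as the primary estimate.
- State that change is measured from the pre-session-1 CRS-R of the same period. Add that score as a covariate, together with the patient's mean of the two period baselines, which keeps between-patient differences out of the within-patient slope. With the pre-treatment score in the model, the treatment coefficient is the same whether the outcome is the post score or the change, so the primary outcome stands.
- Keep the unadjusted change-score model, with its treatment term, as a sensitivity analysis, and say that a difference between the two may reflect carryover.

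The cost is wording and about two degrees of freedom; no new data are needed. The downside is the bias of −(1 − rho)L/2 under a persisting residual effect, which is why the sensitivity analysis is part of the fix.

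### The primary mixed model leaves the within-patient covariance open; if fitted as a plain random patient intercept, the 5% test runs at about 5.7-7% when a patient's two CRS-R changes are uncorrelated or mildly negatively correlated

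*Supplement*

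**What the plan says.** The primary outcome (SAP V2.0, 2.2.1) is the iTBS-sham difference in the change of CRS-R total score after five sessions. Each patient has two treatment periods, so the fifth-session analysis uses two changes per patient. SAP section 6, repeated in protocol V2.0 section 13.2, specifies a linear mixed model with sequence, period, time since injury, etiology and age as fixed effects and "random effects (subjects for repeated measurements"). It does not name a residual covariance, an estimation method or a degrees-of-freedom method. R and SPSS are both listed without saying which fits this model. The subscale and PSD models take the same random part.

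On measurement, SAP section 3 says: "The CRS-R score will be assessed before and after every session of active and sham stimulation within 2 hours". That fixes when scores are taken, not which score is subtracted to form the change. The only CRS-R baseline defined (protocol 8.1) is a single enrolment value, the highest of at least two assessments.

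SAP section 4 states that "enrolling 44 patients would provide 90% power" "to detect a mean difference of 1.2 points (standard deviation [SD] = 1.5"), "accounting for a 15% dropout rate". No within-patient correlation is given there or elsewhere.

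**The concern.** A random intercept with a non-negative variance forces the correlation between a patient's two changes to be zero or above. That is usually harmless for raw scores, because stable differences between patients dominate. In a change score those differences cancel, and what remains can be correlated in either direction. If each change is taken from its own period's starting score, slow fluctuation, or a spontaneous step that falls in only one period, pushes the correlation below zero.

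The fitted intercept variance then goes to zero, the two changes are treated as independent, and the treatment contrast is tested against an error that is too small. The primary P-value and confidence interval are affected. Where there is a departure, it is in the anti-conservative direction.

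**Working it through.** **Inputs from the documents.** Two-sided alpha 0.05; 44 patients; 15% dropout, so 44 x 0.85 = 37.4, about 37 completers; difference 1.2; SD 1.5; 1:1 allocation to two sequences; two changes per patient. **Assumed.** The within-patient correlation rho, examined over a range; treatment added to the fixed effects, since the SAP list omits it and there is no test without it; five covariate degrees of freedom.

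**1. The plan's own figure.** Take 1.5 as the SD of each period's change and rho = 0. The SD of the within-patient difference is 1.5 x sqrt(2) = 2.12. A paired t calculation needs 35 patients (36 if even), and dividing by 0.85 gives 42 (43), close to 44. Power with 37 completers is 91.7%; exactly 90% would imply rho of about -0.07. Taking 1.5 as the SD of the within-patient difference gives 19, inflated to 23. Two parallel arms give 68, inflated to 80. So 44 fits best with rho near zero, although the SAP does not say so.

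**2. Mechanism.** With n patients split equally between sequences, the treatment estimate has variance 2 x sigma^2 x (1 - rho)/n. The within-patient mean square MSW estimates sigma^2 x (1 - rho). The between-patient mean square MSB estimates sigma^2 x (1 + rho). REML with a non-negative intercept variance uses MSW when MSB >= MSW. Otherwise it uses

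(dfB x MSB + dfW x MSW)/(dfB + dfW),

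which is then always smaller than MSW. In large samples with rho < 0 the pooled value tends to sigma^2, so the size tends to 2 x [1 - Phi(1.96/sqrt(1 - rho))]: 6.2% at -0.1 and 7.4% at -0.2.

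**3. Finite-sample size.** Simulation of these mean squares, 400,000 replicates per cell, t reference:

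| rho | intercept set to zero, n=37 / 44 | random intercept, n=37 / 44 | within-patient analysis |
|---|---|---|---|
| +0.3 | 4% / 3% | 5.0% / 5.0% | 5.0% |
| +0.2 | 13% / 11% | 5.2% / 5.0% | 5.0% |
| 0 | 51% / 50% | 5.7% / 5.7% | 5.0% |
| -0.1 | 72% / 74% | 6.3% / 6.3% | 5.0% |
| -0.17 | 84% / 86% | 6.9% / 6.9% | 5.0% |
| -0.2 | 88% / 90% | 7.1% / 7.2% | 5.0% |

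Direct REML fits at n = 37 (4,000 per cell, Monte Carlo error about 0.4 point) gave 4.8% at +0.2, 6.1% at 0, 6.0% at -0.1 and 7.6% at -0.2. The root-mean-square standard error relative to the true one is 0.97 at rho 0, 0.94 at -0.1 and 0.92 at -0.2.

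**4. Which rho is plausible.** For illustration, take a stationary first-order autoregressive score with day-to-day correlation phi, measured on days 1, 5, 11 and 15.

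- Own-period baselines: rho = -phi^6 x (1 - phi^4)/2. The minimum is at phi^4 = 0.6, a decay of about 7.8 days: -(0.465 x 0.4)/2 = -0.093. Independent rating error would move this towards zero.
- One shared day-1 baseline, 7-day decay (phi^4 = 0.565, phi^10 = 0.240, phi^14 = 0.135): rho = (1 + 0.240 - 0.565 - 0.135)/(2 x sqrt(0.435 x 0.865)) = +0.44, where the test is at 5.0%.

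Adding one spontaneous step of 2 to 5 points within 20 days, in up to 90% of patients, to own-period changes gives rho from -0.03 to -0.17. Allowing only one step per patient builds in some of that negative covariance.

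**The case against.** The strongest reply is that nothing here is established without three assumptions: the covariance, the baseline and the sign of rho. All three points have force.

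- **Covariance.** The words on repeated measurements do not exclude a residual structure that permits negative values, such as SPSS REPEATED, and SPSS is listed. A reader might infer that the SAP allows a random intercept and nothing else; the text does not go that far. The intercept is still the natural reading. The cumulative link model is said to use the same random effects, and there a subject effect is ordinarily an intercept. If the words can be run either way, the primary P-value depends on an unwritten choice.
- **Baseline.** The route to a negative rho needs changes from each period's own starting score. That is reasonable in a crossover, but the SAP does not state it. A shared enrolment baseline reverses the sign.
- **Sign.** Patients are enrolled from 15 days to 1 year after injury, in VS/UWS or MCS. Strong differences in steady recovery rate are plausible, would make rho positive, and would bring the two analyses together.

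A reader might also infer that the primary test runs at 6-8% as a matter of fact. The documents do not support that. Reaching 8% needs rho near -0.3 (8.2%), and none of the scenarios examined goes below -0.17.

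**Conclusion.** The point holds as a conditional one. If the model is fitted as a plain random patient intercept, the nominal 5% test runs at about 5.7% at correlation 0, 6.3% at -0.1 and 7% at -0.17 to -0.2. At +0.2 or more it is at 5.0-5.2%. The documents settle neither the correlation nor its sign. Zero or slightly below is plausible with period-specific baselines, and the sample size of 44 sits closest to a correlation near zero, but a shared baseline or patient-specific recovery rates would remove the problem. The inflation is modest. It bears on the trial's single primary test, and a covariance that avoids it holds 4.9-5.1% over the whole range examined, -0.5 to +0.5. This is a worthwhile tightening of the specification, not evidence that the planned test is invalid.

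**What to change.** In SAP section 6 and protocol section 13.2, state that the two period changes are fitted with an unstructured 2x2 within-patient residual covariance, by REML with Kenward-Roger degrees of freedom. Equivalently, compare within-patient period differences between the two sequences. Apply the same to the subscale and PSD models. The same sentence should say which CRS-R score is subtracted to form each change.

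The cost is one line of text and one model option. When the correlation is clearly positive, the estimate and standard error essentially match those of the random-intercept model. Between 0 and about -0.2 the standard error is slightly larger and apparent power is lower. With 37 completers, a difference of 1.2 and SD 1.5 per period, it falls from 93.1% to 91.7% at 0, from 91.6% to 89.1% at -0.1 and from 90.3% to 86.3% at -0.2. With 44 patients the loss is 0.7 to 2.7 points. That power is only apparent, since it comes from a test running above its nominal level.
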